#### Power and sample size

We estimated that a sample size of 500 participants would provide at least
85% power to detect a win ratio and corresponding 95%CI above 1. This
calculation was made based on the following assumptions: (1) a 2% absolute
reduction in hospital mortality from 30 to 28% with dapagliflozin; (2) a 3%
absolute reduction in initiation of KRT from 10 to 7% with dapagliflozin;
and (3) a mean reduction in ICU LOS of 0.5 days with dapagliflozin. The
estimation was obtained after performing 10,000 simulations in samples of
500 participants using these assumptions and 95% confidence intervals
obtained by bootstrapping. Figure 3
displays the results of the obtained lower boundaries of the 95% confidence
intervals of the win ratio values from these simulations.

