### Study procedures

#### Interventions

Eligible patients will be randomized 1:1 to dapagliflozin 10mg plus standard
of care or standard care alone (Figure 1). Randomization is performed centrally through the Research
Electronic Data Capture (REDCap) system,^(24)^ stratified by study site with variable
block sizes of 4, 8 and 12. A confidential randomization list was generated
by the coordinating center. As an open-label study, no procedures to blind
site staff, study personnel, or physicians involved in patient care will be
conducted.

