### Statistical considerations

#### Planned Statistical Analysis

The primary outcome analysis will be conducted using the unmatched win ratio
(WR) method^(27)^ as
proposed by Pocock et al.,^(28)^ with the hierarchical composite primary outcome of (1)
hospital mortality, (2) initiation of KRT, and (3) ICU length of stay-LOS
(in days). The win ratio will be assessed by comparing every possible pair
of participants from the intervention and control groups in a pairwise
descending fashion. A structural framework using nodes in a decision tree
will be used for each level of comparison, with labels of “win” or “loss”
assigned if one participant has a better outcome than the other or a “tie”
otherwise. Hospital mortality will be the primary level of comparison, and
reflecting the higher importance of this outcome, pairwise comparisons in
which both participants die will be determined as an early “tie.” If both
participants survive, they proceed to the second level of the hierarchy for
a comparison of the initiation of KRT. If both participants do not require
KRT, or if both require it, the pair is then moved to the third level to
compare the ICU LOS. For the ICU LOS outcome, the pair with the shorter
duration of stay is considered the “winner.” The structural framework for
the three pairwise comparisons according to the hierarchy of the composite
primary outcome is shown in figure 2.

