**Figure 2 f2:**
[figure not shown]
Flowchart for the win ratio according to the hierarchy of the
primary outcome.

The WR is calculated as the ratio of the total number of “wins” between the
intervention and control groups, and a WR > 1.0 indicates a better
outcome in the intervention group. The 95% confidence intervals (95%CI) for
the WR will be calculated by bootstrapping based on 10,000 samples, and
95%CI not including the unit (1.0) will be considered statistically
significant.

Secondary binary outcomes will be analyzed using a Bayesian hierarchical
logistic regression model. The model will include the study group as a
predictor and will be adjusted for study site, age, clinical suspicion of
sepsis, use of vasopressors, and mechanical ventilation at randomization. A
neutral prior of moderate strength^(29)^ and normal distribution, centered at an odds ratio
(OR) of 1.0 and a standard deviation of 0.35, corresponding to a 95%
probability that the effect (OR) is within the 0.5 - 2.0 range, will be
used. Superiority of the dapagliflozin group over the control group will be
determined if the posterior distribution of the adjusted odds ratio (aOR)
being less than 1.0 [Pr (aOR < 1.0)] is more than 95%. The results will
be presented as the posterior distribution of the aOR (in log scale), a 95%
credible interval, and the probability of the aOR being less than 1.0.

Intensive care unit-free days, hospital-free days, vasopressor-free days,
mechanical ventilation-free days, and KRT-free days will also be analyzed
using a Bayesian hierarchical ordinal model, using the same covariates from
the binary outcomes model. Frequentist analysis exploratory analysis for
secondary outcomes will also be performed, and no p values will be
presented. Binary outcomes will be analyzed thorough a logistic regression
model, with the same covariates as the Bayesian models, and data will be
presented as aOR, crude OR, and corresponding 95%CI. Treatment differences
in free day outcomes will be calculated using the Hodges‒Lehmann method and
presented as the difference in days and 95%CI.

All primary, secondary and safety analyses will follow the intention-to-treat
principle. A sensitivity safety analysis will also be conducted in all
participants who received at least one dose of dapagliflozin (safety
population). Full details of all planned analyses are provided in version
1.0 of the Statistical Analysis Plan (Supplementary Material). All analyses

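### The stated power of at least 85% with 500 participants is not reproduced from its listed assumptions under ordinary distributions of ICU stay

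*Protocol article*

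**What the plan says.** All references are to the protocol article.

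- **Power and sample size** opens: "We estimated that a sample size of 500 participants would provide at least" "85% power to detect a win ratio and corresponding 95%CI above 1". The assumptions are a "reduction in hospital mortality from 30 to 28% with dapagliflozin", an "absolute reduction in initiation of KRT from 10 to 7% with dapagliflozin", and "a mean reduction in ICU LOS of 0.5 days with dapagliflozin". The figure comes from 10,000 simulated trials of 500 with bootstrap intervals. The Figure 3 caption says that the figure shows lower 95% limits of the WR.
- **Planned Statistical Analysis** sets the order: death, then KRT, then ICU LOS, where the shorter stay wins. A pair in which both die is a tie and goes no further.
- **Primary outcome** counts LOS in whole calendar days up to 28 days.
- **Table 1** requires an expected ICU stay of at least 48 hours.

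The article gives no mean, SD or shape for LOS, and no implied WR.

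**The concern.** The assumed mortality and KRT effects are small for 250 per arm, so a half-day difference in ICU stay has to supply nearly all of the power. In a rank-type comparison such as the WR, the value of half a day depends on how tightly stays are bunched. If they are spread over many days, half a day changes few pairwise results.

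This power statement is the article's stated basis for N = 500, and the primary conclusion turns on whether the 95% CI excludes 1. If power is well below 85%, a CI that includes 1 is a likely result even when all three assumed effects are true. Readers told that power was at least 85% would take such a CI as evidence against those effects.

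**Working it through.** **Inputs from the article.** 250 per arm (500 participants, allocated 1:1); two-sided 95% CI; mortality 30% control, 28% dapagliflozin; KRT 10% and 7%; LOS 0.5 days shorter; both-dead pairs tied.

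**Assumptions made here.** The KRT rates apply among survivors, LOS is independent of KRT, and the LOS distribution is varied because none is stated.

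**1. Where pairs are decided**
- Death: wins 0.72 × 0.30 = 0.216; losses 0.28 × 0.70 = 0.196; together 41.2%.
- Both dead (tie): 0.28 × 0.30 = 8.4%. Both alive: 0.72 × 0.70 = 50.4%.
- KRT: wins 0.504 × 0.93 × 0.10 = 0.0469; losses 0.504 × 0.07 × 0.90 = 0.0318; together 7.9%.
- Reaching LOS: 0.504 − 0.0786 = 0.4254, or 42.5%.

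**2. No LOS effect.** Split the LOS pairs evenly, 0.2127 each way:

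WR = (0.216 + 0.0469 + 0.2127) / (0.196 + 0.0318 + 0.2127) = 0.4756 / 0.4404 = 1.08.

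The simulated SE of log WR is 0.112-0.118. With 0.1125, power = Φ(ln 1.08 / 0.1125 − 1.96) ≈ 10%. Direct simulation gives about 11%.

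**3. What 85% requires.** WR = exp((1.96 + 1.036) × 0.1125) = 1.40. Let p be the share of LOS comparisons won:

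(0.2629 + 0.4254p) / (0.2278 + 0.4254(1 − p)) = 1.40, so p ≈ 0.64.

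**4. What a 0.5-day shift gives.** For normal LOS, p = Φ(0.5 / (SD × √2)). The formula column uses SE 0.1125. The simulation column gives the range over independent runs, some with LOS rounded to whole days.

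| LOS SD, days (assumed) | p | WR | Power, formula | Power, simulated |
|---|---|---|---|---|
| 1 | 0.638 | 1.40 | 85% | 80-86% |
| 1.5 | 0.593 | 1.29 | 61% | 58-62% |
| 2 | 0.570 | 1.23 | 45% | 44-48% |
| 3 | 0.547 | 1.18 | 31% | 29-33% |
| 5 | 0.528 | 1.14 | 21% | 18-23% |
| 8 | 0.518 | 1.12 | 16% | 15-18% |

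The article's 85% is therefore recovered with a normal SD of about 1 day. A percentile bootstrap agreed with these intervals within 1 point in six scenarios.

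**5. Other shapes (all assumed)**
- Gamma in whole days, mean 7, SD 5: 20-22%.
- Lognormal in whole days, mean 5, SD 5: about 24% with a proportional reduction, up to 38% with an additive shift.
- Poisson, mean 5: 41-43%.
- Lognormal in whole days, mean 3, SD 3, additive shift: 56%.
- Lognormal, mean 3, SD 2: up to 64%.
- Poisson, mean 1.5: 75%.
- Tight core with a tail (85% of stays near 3 days with SD 0.7, 15% in a tail to 28 days; overall mean 4.7, SD 4.6): 86% continuous, 82% in whole days. A similar mixture gave 87% and 78%.

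**6. Other readings of the text (normal LOS)**
- One-sided 5%: 23-43% at SDs of 3-8 days.
- Both-dead pairs not tied: 19-36% at SDs of 3-7 days.
- 500 per arm: 50% at SD 3 and 36% at SD 5.

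**The case against.** The strongest reply is that the decisive input is not in the article. The LOS distribution may be in the SAP or full protocol, Figure 3 is not shown in the text reviewed, and an article may leave simulation parameters to those documents. That stands in part: the simulation is not proven wrong, and the absence of an SD is not itself the fault. But the article offers 85% as the result of three listed effects, and no ordinary LOS shape tried here delivers it. Whatever the SAP states would have to bunch most stays within about a day of each other.

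Three stronger readings are tempting and are not supported:

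- **That 85% is impossible unless the SD of LOS is about 1 day.** This holds for a normal-type shift only. The tier works on ranks, so bunching matters rather than the SD, and the tight-core mixture reaches 86% with an overall SD of 4.6 days.
- **That the true power is 15-30%.** That range fits normal LOS with SDs of about 3-8 days. Short or strongly skewed stays give more, and the result moves with how the half day is applied.
- **That the simulation counted trials with a point estimate above 1.** At SDs of 3-7 days that probability is about 83-93%, which sits near the stated figure. But the text and the Figure 3 caption both refer to the confidence interval, and nothing in the article shows otherwise.

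**Conclusion.** The concern holds as a failure to reproduce. Power of 85% needs a true WR of about 1.40. The mortality and KRT effects bring the WR only to about 1.08, and a 0.5-day shift makes up the rest only when stays are very tightly clustered. Such clustering fits poorly with a mixed ICU population expected to stay at least 48 hours and counted to 28 days.

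Under assumed smooth LOS shapes, power is roughly 15-35% at SDs of 3-8 days and up to about 40-60% for short or strongly skewed stays. Only very short stays, such as Poisson with mean 1.5, come closer. These figures depend on LOS distributions that the article does not give. The two results that do not depend on LOS shape are the 10% from mortality and KRT alone and, within the small range of the SE, the WR of about 1.40 needed for 85%.

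**What to change.** Keep N = 500 and correct the statement in Power and sample size:

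1. Rerun the simulation with a stated LOS distribution: mean, SD, shape, whole-day ties, and whether the 0.5-day effect is additive or proportional.
2. Inform that distribution with pooled, arm-blind LOS data from enrolled participants. The article reports 100 enrolled by the first safety analysis in March 2023.
3. Report the implied WR, and replace the claim of at least 85% with the recomputed figure.
4. Add that 500 participants give 85% power for a WR of about 1.40.

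The power figures above for assumed distributions should not be copied into the protocol; they show sensitivity only. The cost is one rerun of an existing simulation and one amended paragraph, with no added participants and no change to the analysis. The downside is that the stated power will probably be less favourable.

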**Figure 3 f3:**
[figure not shown]
Lower boundary of the win ratios 95% confidence intervals
obtained through 10,000 simulations on samples of 500
patients.

### Interim analysis and Data and Safety Monitoring Board

The DSMB regularly reviews unblinded patient-level data during the study to
ensure participant safety. The first safety analysis occurred on March 27, 2023,
after 100 participants were enrolled. An interim analysis will occur when half
of the sample size (n = 250) has been enrolled and followed for at least 14
days. For this specific analysis, trial recruitment will be halted for four
weeks and will resume only after the DSMB deliberation. Another safety analysis
is planned to occur after 375 participants are enrolled. The sole purpose of the
interim analysis is to assess safety, and the trial will not be halted for
benefit or futility. The frequency of safety interim analysis might be changed
if deemed appropriate by the DSMB members.

At the interim analysis, the DSMB will use a Bayesian framework (simple logistic
regression) to assess the posterior probability distribution for harm (OR >
1.0) for hospital mortality and initiation of KRT. If this probability is
greater than 80%, the DSMB will recommend stopping the trial. Harm will also be
assessed in two key subgroups: participants with hypotension or acute kidney
injury at randomization. If the probability of harm is greater than 80% for
either subgroup, the DSMB will recommend excluding them from the trial.

Additional interim analyses may be convened at the discretion of any DSMB member
if new scientific data or concerns arise during the study, especially regarding
the ongoing SGLT2i arms of the ACTIV-4A (NCT04505774) and RECOVERY (NCT04381936)
platform trials. Based on the interpretation and quality of the data, the number
of events, and other factors, the DSMB may recommend modifications to the
protocol (e.g., changes to inclusion/exclusion criteria), suspension, or
termination of the trial, and advise the Steering Committee. However, all final
decisions regarding trial conduct will be at the discretion of the Steering
Committee.

### Current status

The first participant was randomized in November/2022, and there are currently 14
active and 13 enrolling sites. The list of active and enrolling sites is updated
on a monthly basis and can be accessed publicly on the study clinicaltrials.gov
webpage.

## DISCUSSION

DEFENDER will be the first study to test the hypothesis that SGLT2 inhibitors can
reduce organ dysfunction and mortality of critical illness from different
etiologies. This approach is different from that of several other randomized
clinical trials that failed to demonstrate improved outcomes in ICU patients, such
as the use of vitamin C^(30-32)^ and statins for
sepsis,^(33)^ probiotics for
ventilator-associated pneumonia,^(34)^ among others.^(35)^

Sodium-glucose cotransporter-2 inhibitors have been used in more than 45,000
participants in over 13 large-scale trials, and the evidence overwhelmingly suggests
that the cardiovascular and kidney benefits outweigh the low risk of serious
harm.^(25)^ It is
biologically plausible that the effects of drugs in this class may positively impact
pathways of organ dysfunction during acute critical illness.^(36)^ Furthermore, the initiation of
SGLT2 inhibitors in hospitalized patients with acute heart failure during
placebo-controlled randomized clinical trials was safe and did not increase the risk
of hypotension, hypoglycemia, or acute kidney injury.^(26)^

Given that this is the first time that SGLT2 inhibitors will be used in general ICU
patients, we have implemented a series of safety measures to minimize potential
risks and preventable harm for current and future study participants that will
permit a comprehensive understanding of the risk/benefit profile of dapagliflozin in
critically ill patients. In conclusion, DEFENDER presents a new approach to evaluate
the potential of SGLT2 inhibitors in reducing organ dysfunction and mortality in
critically ill patients and will provide valuable information for future trials in
this population.
